### Sociodemographic data

Parents filled out a demographic sheet for themselves and their children, on age, gender, ethnicity, and race. Additional questions for parents included marital and employment status, socioeconomic status and education level. Additional questions for parents to answer about their children included their birth order and health status.

### Weight outcomes

Height was measured on all children and parents in street clothes without shoes, using a stadiometer, calibrated in 1/8-cm (cm) intervals. Height was measured twice and averaged. Weight on all children and parents was measured in a private room, in street clothes without shoes, to the nearest 0.1 kg using a Tanita WB-110A Digital Scale.

For children, BMI percentiles were calculated twice by entering height, weight, age, and gender [49]. Children with a BMI ≥ 85^th ^and < 95^th ^percentile for age and gender were considered overweight, and those at or above the 95^th ^percentile were obese [49]. BMI of parents was calculated twice by entering height and weight (kg/m^2^) [49]. In adults age 20 years and older, overweight was defined as a BMI between 25.0 and 29.9, and obesity was defined as a BMI equal to or greater than 30.0 [49].

### Adiposity outcomes

Waist circumference was measured in a privately screened area by two RAs, following the procedure used in the Insulin Resistance Atherosclerosis Study, using a Figure Finder measuring tape with lock (Novel Products Inc., Rockton, IL) [50]. All measurements were performed three times and averaged according to the National Health and Nutrition Examination survey procedures [51,52].

Using Lange skinfold calipers, triceps and subscapular skinfolds were measured in children and parents on the right side of the body three times and averaged, also according to the National Health and Nutrition Examination survey procedures [51,52]. To ensure reliability, prior to each data collection, RAs were tested for inter-rater reliability by calculating correlations when measuring skinfolds on the same participants.

### Health behavior outcomes

The 23-item Adult Health Behavior Survey [53] and the 20-item Child Health Behavior Survey [53] were used to collect information on intake of sugared beverages, juices, fruits, vegetables, whole grains, fried, baked and fast foods on a daily or weekly basis. Responses are scored from 0 = none or never to 5 = 5 or more. Alpha coefficients in children range from 0.79 to 0.80 and in parents from 0.80 to 0.86 [53].

The Health Promoting Lifestyle Profile II (HPLP II) was used to measure health promoting lifestyle behaviors in parents [54]. This 48-item, 4-point Likert scale questionnaire with 4 response choices: never, sometimes, often, or routinely, measures the frequency of health promoting behaviors in six subscales. Only four subscales (health responsibility, exercise, nutrition, and stress management) were used in this study; the communication and spirituality subscales were not used. The instrument has been used with both minority and white populations [54]. Alpha coefficients ranged from 0.78 to 0.93 for the subscales. Test-retest reliabilities in African American women have ranged from 0.70 to 0.74 [57].

The Child and Adolescent Trial for Cardiovascular Health (CATCH) questionnaire was used to measure children's diet and exercise health behaviors and self-efficacy [55]. The instrument contains 130 forced-choice items on a 3-point Likert scale in seven subscales: exercise, dietary knowledge, dietary intentions, dietary choices, support, social reinforcement, and self-efficacy. Alpha coefficients ranged from 0.76 to 0.84 in a sample of 5,000 children [55]. The questionnaire is at a 2rd grade reading level and takes approximately 15 min to complete [40]. Alpha coefficients for the subscales ranged from 0.87 to 0.90 in our pilot study [40].

### Self-efficacy outcomes

The Eating Self-Efficacy Scale [56] was used to measure self-efficacy related to dietary changes in parents. This 25-item instrument asks participants to rate their difficulty in controlling eating from 1 (no difficulty) to 7 (difficulty) on two subscales, negative affect (NA) and socially acceptable circumstances (SAC). Negative affect eating is related to emotional eating and the triggers that cause it (e.g., anger or anxiety). Socially acceptable eating is related to overeating at parties, family events, or holidays. Scores range from 25 to 175, with higher scores indicating more difficulty in controlling eating. Alpha coefficients were 0.94 for the NA subscale and 0.85 for the SAC subscale. Test-retest reliability was 0.70 in a sample of 600 women and men [56].

Exercise self-efficacy in parents was measured using Bandura's Exercise Self-Efficacy Scale with 18 questions on a 100-point scale, ranging in 10-unit intervals from 0 (cannot do at all) through intermediate degrees of assurance such as 50 (moderately certain can do) to 100 (certain can do) [33]. The questions are added up and divided by 18 to calculate a total Exercise Self-Efficacy score [33]. A higher score indicates greater self-efficacy. Alpha coefficients of the total scale ranged from 0.86 to 0.92 in adult men and women [58].

### Data analysis plan

An intent-to-treat analysis will be used in which all participants are analyzed according to their initial randomized assignment, whether they receive the intervention regularly or not, to preserve the balance of covariates due to randomization and to provide a conservative analysis that does not overestimate intervention effectiveness. Random baseline differences will be accounted for with this approach.

#### Aim 1

To determine the effects of the intervention on weight status, adiposity, health behaviors and self-efficacy, general linear mixed models will be used. Separate random coefficients models will be used to test each outcome for longitudinal differences between the experimental and wait-listed control groups. Advantages of the mixed model approach include its ability to incorporate data from visits that are mistimed as well as certain missing data structures, so that participants who miss one or more visits need not be excluded from the analysis. In addition, random coefficient models accommodate both categorical and continuous covariates.

If a characteristic is found to differ between the groups at baseline, it will be included as a covariate to account for this random imbalance. Additionally, recognizing that certain factors could influence our dependent variables, whether or not they are randomly imbalanced in the two groups, we will control for them as covariates in the models. These variables include asthma, diabetes, low-dose steroids, psychiatric medications (e.g., amitriptyline), cardiac medications (e.g., beta blockers), and recent smoking cessation.

#### Aim 2

The relationships between experimental child changes in weight status, adiposity, health behaviors, and self-efficacy and experimental parent changes in weight status, adiposity, health behaviors, and self-efficacy will also be addressed via the general linear mixed model. Each outcome will be analyzed through a separate random coefficient model. The models will be structured in a fashion similar to that described for Aim 1, but with a different set of predictor variables, in order to examine the associations between improvements in parents and their children. For each model, the children's baseline values for the outcome will be included as a covariate.

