### Power analysis

Power calculations were performed with POWERLIB20 SAS/IML modules [38]. These methods calculate power for the general linear multivariate model, which includes repeated measures data structures, of which a two-group longitudinal design is a special case. Power was based on a separate multivariate model for each outcome addressed in the aims, incorporating measurements from all time points. Models were derived separately for children and parents. The power analysis focused on one representative variable in each group of variables, BMI percentiles (children) and BMI (parents) for weight status, waist circumference (children and parents) for adiposity, the Child and Adolescent Trial for Cardiovascular Health (CATCH) nutrition knowledge subscale (children) and the Health Promoting Lifestyle Profile II nutrition knowledge subscale (parents) for health behaviors, and the Child and Adolescent Trial for Cardiovascular Health (CATCH) self-efficacy subscale (children) and the Eating Self-Efficacy Scale subscale (parents) for self-efficacy. On the basis of pilot data, the autoregressive correlation parameter was chosen as 0.99 for parents' BMI, 0.90 for children's BMI and parents' and children's waist circumference, and 0.84 for the health behavior and self-efficacy variables. Effect sizes used were based on studies with similar designs using the dependent variables of interest. Given the clustered nature of the design (with each site-by-condition classification considered a cluster), an intracluster correlation coefficient of 0.01 was selected (based on BMI). A total of 179 child-parent pairs per group or a total of 358 children and 358 parents have been inducted.

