### Measurement

Table 1 shows the variables and measures being used in the study, the data source, and measurement times. Data are being collected at Time 1 (Baseline), Time 2 (Post Phase I-Intensive Intervention), Time 3 (Post Phase II-Continued Support), and Time 4 (6-Months After Completion of Phase II). All instruments were evaluated for psychometric properties before the pilot study, were re-evaluated during the pilot study, and will be re-evaluated in this study. Completion of measures takes approximately 60 min for most children and parents.

**Table 1 T1:** Summary of measures

Variables and Their Measurement	Respondent	T1	T2	T3	T4	Alpha	Reference
Weight Status Outcomes							

Height	Child/Parent	X	X	X	X	-----	[49]

Weight	Child/Parent	X	X	X	X	-----	[49]

Body Mass Index Percentiles Calculation	Child	X	X	X	X	-----	[49]

Body Mass Index Calculation	Parent	X	X	X	X	-----	[49]

Adiposity Outcomes							[49]

Waist Circumference	Child/Parent	X	X	X	X	-----	[50]

Triceps and Subscapular Skinfolds	Child/Parent	X	X	X	X	-----	[51,52]

Health Behavior Outcomes							

Health Behavior Survey	Child/Parent	X	X	X	X	0.79-0.86	[53]

Health Promoting Lifestyle Profile II	Parent	X	X	X	X	0.78-0.93	[54]

Self-Efficacy Outcomes							

Child and Adolescent Trial for Cardiovascular Health	Child	X	X	X	X	0.87-0.90	[55]

Eating Self-Efficacy Scale	Parent	X	X	X	X	0.88-0.94	[56]

Exercise Self-Efficacy Scale	Parent	X	X	X	X	0.86-0.92	[33]

Sociodemographic Data	Parent for Self and Child	X				-----	-----

T1 (Baseline); T2 (Post Phase I-Intensive Intervention); T3 (Post Phase II-Continued Support); T4 (6-Month After Completion of Phase II)

To ensure inter-rater reliability during the course of the study, RAs were trained and tested for inter-rater reliability prior to each data collection on height, weight, waist circumference, triceps and subscapular skinfolds. During data collection, a duplicate measures program was implemented for quality control testing. Every 10th participant had height, weight, waist circumference, triceps and subscapular skinfolds repeated by a second RA. These data were analyzed monthly to assess reliability and if reliability was not adequate, the RAs were retrained. All data collection RAs were blinded to the study group assignment.

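### Aim 1 does not fix adjustment for each outcome's own baseline value: as written, it becomes a covariate only if the arms are found to differ at T1

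*Protocol article*

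**What the plan says.** All references are to the protocol article.

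- **Data analysis plan, Aim 1, model:** "Separate random coefficients models will be used to test each outcome for longitudinal differences between the experimental and wait-listed control groups". The group and time terms are not written out.
- **Aim 1, conditional adjustment:** "If a characteristic is found to differ between the groups at baseline, it will be included as a covariate to account for this random imbalance".
- **Aim 1, covariates used regardless of balance:** "These variables include asthma, diabetes, low-dose steroids, psychiatric medications (e.g., amitriptyline), cardiac medications (e.g., beta blockers), and recent smoking cessation". The outcome's baseline value is not among them.
- **Data analysis plan, opening paragraph, on intention to treat:** "Random baseline differences will be accounted for with this approach". No mechanism is given.
- **Data analysis plan, Aim 2:** "For each model, the children's baseline values for the outcome will be included as a covariate".
- **Power analysis:** the autoregressive parameter is "0.99 for parents' BMI, 0.90 for children's BMI and parents' and children's waist circumference, and 0.84 for the health behavior and self-efficacy variables". The lag to which it applies is not stated. The power models use measurements from all time points.
- **Measurement and Table 1:** every outcome is scheduled at T1. "Data are being collected at Time 1 (Baseline), Time 2 (Post Phase I-Intensive Intervention), Time 3 (Post Phase II-Continued Support), and Time 4" is the visit schedule.

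**The concern.** The baseline value of an outcome is usually its strongest predictor, and here the power section itself assumes high serial correlation. Aim 1 nevertheless commits to adjusting for conditions and medications whose link to the outcomes is not quantified, and leaves the baseline outcome to a rule that looks at the data first. Two consequences follow.

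1. **The rule is not triggered.** In a model with T1 among the responses and a free arm difference at T1, the arm-by-time effect is in substance a difference in change. Precision that the collected data could give is then lost.
2. **The rule is triggered.** T1 becomes a covariate. If it is also a response, as the all-time-points power model and the baseline-to-18-month outcome definition suggest, the same measurement sits on both sides of the model.

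At stake are the efficiency of the child primary test and the secondary tests, and a model form that depends on the observed baseline data.

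**Working it through.** **What cannot be reproduced.** The article gives 179 pairs per group but no alpha, target power or effect size, so the sample size cannot be recomputed. An article may leave these to the full protocol; this is not part of the point. Two-sided alpha 0.05 and 80% power below are my assumptions.

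**Inputs from the article.** Autoregressive parameters 0.99, 0.90 and 0.84; four visits (0, 12 weeks, 12 months, 18 months); ICC 0.01; 358 pairs; eight induction periods of two schools, so 16 site-by-condition clusters.

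**Formulas.** Let r be the T1-to-T4 correlation and s² the outcome variance, equal at both visits.
- Change-type contrast: variance proportional to 2(1 − r)s².
- Baseline-adjusted contrast: variance proportional to (1 − r²)s².
- Ratio, adjusted to change: (1 − r²) / [2(1 − r)] = (1 + r)/2.
- Power after adjustment = Φ[(1.96 + 0.842)/√ratio − 1.96].

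Clustering is taken to inflate both variances equally and so to cancel.

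**Main case: parameter applied per visit, so T1 to T4 is three lags.**

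| Outcome | r | Ratio | Power from 80% |
|---|---|---|---|
| Parent BMI | 0.99³ = 0.970 | 0.985 | 80.6% (+0.6) |
| Child BMI percentile | 0.90³ = 0.729 | 0.865 | 85.4% (+5.4) |
| Behaviour, self-efficacy | 0.84³ = 0.593 | 0.796 | 88.1% (+8.1) |

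Waist circumference shares the 0.90 parameter and so the child BMI percentile row.

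**Sensitivity (child BMI percentile; behaviour and self-efficacy), in power points.**
- Parameter read as the full 18-month correlation: 2.0; 3.2.
- Parameter read as a 3-month correlation: 9.3; 12.6.
- Main case, but the adjusted test placed at 80% and the loss counted downwards: 5.9; 9.5.
- 3-month reading with the adjusted test at 80%: 11.2; 16.6 (16.9 for a linear slope). These are the upper ends.
- Main case with the unadjusted test at 90%: 3.7; 5.3.
- Linear slope over the four visits, per-visit parameter: 4.7; 7.1.
- t test with 14 degrees of freedom for 16 clusters: 5.4; 8.1, unchanged.
- Parent BMI runs from 0.2 (18-month reading) to 1.2 (3-month reading).
- Common T1 mean for both arms: this is already the efficient model, so the loss is 0.

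**Same loss as a detectable difference.** Cluster size is 358/16 = 22.4, design effect 1 + 21.4 × 0.01 = 1.21, effective n per arm 179/1.21 ≈ 147. At 80% power the detectable difference is 0.240 SD unadjusted against 0.223 SD adjusted for child BMI percentile, and 0.294 against 0.263 SD for behaviour and self-efficacy.

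**Chance baseline gap.** A change contrast carries the fraction 1 − r of a baseline gap into the estimate: 27% for child BMI percentile, 41% for behaviour. Since 2(1 − r) = (1 − r²) + (1 − r)², this carry-over is exactly the extra variance counted above (child: 0.542 = 0.469 + 0.073). It is also small. The SD of the gap is √(2 × 1.21/179) = 0.12 SD, or about 0.75 points with the SD of 6.4 in Table 3, so the carry-over is about 0.2 points.

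**The case against.** **The model terms are simply not given.** An article may leave them to the full protocol or SAP, and a common T1 mean would make the loss zero. This stands as a limit on the size: nobody can say from the article that the Aim 1 test is change-score-like. It does not remove the point, because the article does state a covariate rule, and that rule makes the outcome's baseline a data-driven covariate.

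**A reader might infer that Aim 1 never adjusts for baseline.** The documents do not support that. The imbalance rule can cover a baseline outcome, and T1 appears to be one of the repeated responses.

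**A reader might see a contradiction with Aim 2.** There is none. Aim 2 is an association between parent and child changes within the experimental group, and adjusting there does not oblige the randomised comparison to do the same. It shows only that the option was in view.

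**A reader might count the carry-over of a chance baseline gap as a second harm, or as bias.** It is the same variance seen another way. Over repeated randomisations the change contrast is unbiased. Each site also serves both conditions in turn, which should help balance stable site differences.

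**The power figures borrow the autoregressive structure from the power section**, whereas Aim 1 names random coefficients models. There the gain depends on the intercept-slope covariance, which the article does not give. This stands: the figures show the order of size and do not predict this trial's power.

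**Conclusion.** The concern holds in a limited form. Aim 1 does not fix adjustment for the outcome's own baseline, and the rule that could bring it in depends on the data and may put T1 on both sides of the model. Given a free arm difference at T1, two-sided alpha 0.05, 80% power for the unadjusted test and a per-visit autoregressive parameter, about 5 power points for child BMI percentile and 8 for behaviour and self-efficacy are lost unnecessarily. Parent BMI, the other primary outcome, is practically unaffected. None of those conditions is stated in the article, so the ranges matter more than the central figures. Nothing here shows that 358 pairs are too few, that the type I error rate is wrong, or that the planned test is invalid. The case for change is that a better-defined analysis is available from data already collected.

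**What to change.** For every Aim 1 outcome, pre-specify baseline adjustment whether or not the arms differ at T1, in one of two forms:

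- keep T1 as a response and fit a common T1 mean for both arms, with arm-by-visit terms only; or
- take T2 to T4 as responses and include T1 as a covariate, with baseline-by-visit terms.

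Report the 18-month arm contrast from the chosen model. State that the imbalance rule does not apply to the outcome's own baseline, so that T1 is never both response and covariate. If a common-baseline model is already intended, saying so and adding this exclusion settles the point.

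The cost is a sentence or two in the analysis plan, with no new data or participants. The one drawback is that in the T2-to-T4 form a participant without a T1 value, or without any later visit, drops out. The common-mean form avoids this.

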## Methods

### Design

Family Partners for Health is a 5-year cluster randomized controlled trial with a two-group repeated measures design (See Figure 1). The sample consists of African American (63%), non-Hispanic white (32%), and bilingual Hispanic (5%) low-income, 2^nd ^to 4^th ^grade overweight or obese children and their overweight or obese parents from small towns and rural areas of North Carolina. An experimental group of children and parents are receiving a two-phase intervention with follow-up. In Phase I (Intensive Intervention) they receive 60 minutes of nutrition and exercise education and coping skills training and 45 minutes of exercise training once a week for 12 consecutive weeks. In Phase II (Continued Support) they meet for 9 monthly meetings. They are then followed for 6 months after the completion of Phase II to assess the maintenance of results (follow-up), for a total of 18 months in the trial. The experimental children and parents have data collected at 4 time points: Time 1 (Baseline), Time 2 (12 weeks: Post Phase I-Intensive Intervention), Time 3 (12 months: Post Phase II-Continued Support), and Time 4 (18 months: 6-months of follow-up).

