### Settings

Eight elementary schools are being used as sites during early evening hours for recruitment and delivery of the intervention. Four schools are located in Wilson, North Carolina, and four in Burlington, North Carolina. The sites are similar in structure, size, and rural, ethnic and racial mix. Each site has classroom space with tables and chairs that are being used for the education and coping skills training classes and a gymnasium that is used for the exercise classes.

There have been eight induction periods over the course of the trial. Forty-four to 45 children and 44-45 parents in two schools (experimental and wait-listed control group) have been enrolled in each period, for a total of 358 children and 358 parents. Each site was randomly assigned to either the experimental or wait-listed control group the first time a cohort was enrolled. The second time that the site had children and parents enrolled, the opposite condition was assigned.

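### The trial was sized with site-by-condition clusters, but the Aim 1 models are described without a term for them, so standard errors would be too small if change varies by cohort

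*Protocol article*

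**What the plan says.** The Design section is explicit about the type of trial: "Family Partners for Health is a 5-year cluster randomized controlled trial with a two-group repeated measures design". The Settings section gives the unit of assignment: "Each site was randomly assigned to either the experimental or wait-listed control group the first time a cohort was enrolled". It then adds: "The second time that the site had children and parents enrolled, the opposite condition was assigned". Eight schools used once in each condition make 16 cohorts, eight per arm. Recruitment agrees with this, with eight induction periods of two schools each: "Forty-four to 45 children and 44-45 parents in two schools (experimental and wait-listed control group) have been enrolled in each period".

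The Power analysis section takes the same cohorts as its clusters, "with each site-by-condition classification considered a cluster", and reports that "an intracluster correlation coefficient of 0.01 was selected (based on BMI". The final size is stated as "A total of 179 child-parent pairs per group or a total of 358 children and 358 parents have been inducted".

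The Data analysis plan then describes the Aim 1 model: "Separate random coefficients models will be used to test each outcome for longitudinal differences between the experimental and wait-listed control groups". It justifies the mixed model by its handling of mistimed visits, missing data and covariates. It lists individual covariates, down to medication classes. It mentions no school, cohort, induction period, cluster random effect, robust variance or cluster-level degrees of freedom. Aim 2 follows the Aim 1 structure with other predictors. The exploratory aim refits the Aim 1 models and adds only ethnicity terms and their interactions with the intervention.

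**The concern.** Allocation is by cohort, and the experimental families are also taught together in school classes. Two families in one cohort may therefore change more alike than two families from different cohorts. The power analysis allows for this and the described analysis does not. A random coefficients model whose only random effects belong to participants treats the 358 pairs as independent, and it takes its degrees of freedom from participants and not from 16 cohorts.

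At stake are the standard errors, intervals and p-values of every Aim 1 outcome, including child BMI percentile and parent BMI, and of the later aims that reuse the models. The section on intention to treat presents the analysis as conservative. Leaving out the clusters would push the other way.

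**Working it through.** **What can be reproduced.** 2 x 179 = 358, and 8 periods x 44 to 45 = 352 to 360, so the counts agree. The sample size itself cannot be reproduced, because the article gives no numeric effect size, alpha or target power. A two-sided alpha of 0.05 is assumed below.

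**Inputs.** 16 clusters (Settings, Power analysis); 358 pairs (Power analysis); ICC 0.01 (Power analysis); serial correlation 0.99 for parents' BMI and 0.90 for children's (Power analysis).

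**Step 1: the document's ICC, taken to apply to change.**
- Mean cluster size m = 358/16 = 22.375.
- Design effect DE = 1 + (m - 1) x ICC = 1 + 21.375 x 0.01 = 1.214.
- Effective n = 358/1.214, about 295.
- Correct SE / unadjusted SE = sqrt(1.214) = 1.102, so the unadjusted SE is 1 - 1/1.102, about 9% too small.
- True type I error = 2[1 - Phi(1.96/1.102)], about 7.5%.
- With 16 clusters in two arms the reference distribution is t on 14 df, with critical value 2.14. An unadjusted p of 0.05 becomes about 0.097. The 95% interval widens by (2.145/1.960) x 1.102 = 1.206, about 21%.

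A simulation of person-level slopes (16 clusters of 22 or 23, 8,000 runs) gave 7.6% for the test that ignores clusters and 5.0% for a t-test on cluster means.

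**Step 2: other ICCs of change (assumed).**

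| ICC of change | DE | Type I error, clusters ignored |
|---|---|---|
| 0 | 1.000 | 5.0% |
| 0.005 | 1.107 | 6.3% |
| 0.01 | 1.214 | 7.5% |
| 0.02 | 1.427 | 10.1% |
| 0.05 | 2.069 | 17.3% |

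**Step 3: what cancels.** A cluster effect that is constant over time drops out of a difference in change; with no cluster variance in slopes the simulation gave 4.8%. A site effect shared by a school's two cohorts cancels between arms. Splitting the 0.01 into a site part s and a site-by-condition part c, the true variance is proportional to 0.99 x 2/179 + c x 2/8, against 2/179 for the unadjusted test:
- s = 0.01, c = 0: SE ratio 0.995, type I error 4.9%.
- s = c = 0.005: SE ratio 1.05, type I error 6.2%.
- s = 0, c = 0.01: SE ratio 1.102, type I error 7.5%.

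**Step 4: from level to change.** If the 0.01 is an ICC of level, then ICC of change = 0.01(1 - rc) / [0.01(1 - rc) + 0.99(1 - rp)]. Here rp is the participant correlation from baseline to 18 months, three visit steps (0.99^3 = 0.970 for parents, 0.90^3 = 0.729 for children), and rc is the cluster-level correlation, which is assumed because the article does not give it.

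| rc (assumed) | Parent BMI: ICC of change | Child BMI percentile: ICC of change |
|---|---|---|
| 0.80 | 0.064 | 0.007 |
| 0.97 | 0.010 | 0.001 |
| 0.99 | 0.003 | below 0.001 |

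For children the first two rows give type I errors of about 6.9% and 5.3%. For parents the range runs from slight inflation to more than the last row of Step 2.

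**Step 5: room for fixed blocks.** Fixed school and induction-period effects use 8 + 8 - k parameters, where k is the number of unconnected groups of schools and periods, and treatment uses one more. If the same four school pairs recur, k = 4 and 16 - 12 - 1 = 3 df remain (critical value 3.18). If all schools and periods are linked, k = 1 and 16 - 15 - 1 = 0 remain.

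**The case against.** The strongest objection is that the point is read from silence in a condensed article. A general linear mixed model can carry a cohort effect. The text never says that its random effects are for participants only, and the power analysis shows that the authors knew of the clustering. Random-effect levels and degrees-of-freedom methods often sit in a fuller plan.

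Part of this stands. A reader might infer that clustering will be ignored and that the standard errors will be too small. The article supports neither as fact. What remains is that the section goes into detail, naming covariates and giving its reasons for a mixed model, and none of that covers the clusters the trial was sized on. A model fitted from that description would leave them out.

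The second objection concerns size, and it also stands. The 0.01 is based on BMI and is not said to be an ICC of change, and time-constant and pure site effects cancel. A reader might also infer errors of 13% to 17% for both primary outcomes. Those figures need ICCs of 0.03 to 0.05, which the article does not contain, and with the cluster-level correlations assumed in the working the child outcome comes out far lower. The cancellation does not, however, remove effects specific to one cohort's class or calendar period, and the article itself defines the cluster as site-by-condition and not as site.

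**Conclusion.** The concern holds as a conditional mismatch between design and analysis. The trial assigns cohorts and was sized on 16 site-by-condition clusters, while the models for Aim 1, and the aims built on them, are described without a term for those clusters.

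If they are fitted as described and change varies by cohort, standard errors are too small. The central figure, an SE about 9% too small and a type I error of about 7.5%, rests on three assumptions: a nominal two-sided 5% level, an ICC of 0.01 that applies to change, and all of it lying at site-by-condition level. Without cohort-by-time variance the error returns to about 5%. With an ICC of change above 0.01, which is more plausible for parent BMI than for child BMI percentile, it is larger. The effect at 0.01 is modest, but it is enough to turn a borderline result, and it bears on both primary outcomes.

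**What to change.** State in the Data analysis plan that the Aim 1 models include a random intercept and a random time effect for the 16 site-by-condition cohorts, with Kenward-Roger or Satterthwaite degrees of freedom. A random intercept alone is not enough, because the tested effect is a difference in change. Carry the terms into Aim 2, where only the eight experimental cohorts contribute, and into the exploratory aim. Report the observed ICCs. As a check, run a t-test on the 16 cohort mean changes.

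School may enter as a random effect, since each school serves in both arms. School and induction period should not both be fixed blocks, because that leaves 3 or 0 cluster-level degrees of freedom.

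The cost is a few lines of text and model code; school and cohort membership are already known. Intervals become somewhat wider, by about 21% at an ICC of 0.01 with 14 df. About 9 points of that come from the t reference alone (2.145/1.960 = 1.094).
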